## 4. Collection to Date

From April 2018 until March 2020, 244 women have been included in the biobank. The biobank is an ongoing project that will continuously enrol women with pre-eclampsia and controls with yearly updates to the local Health Research Ethics Committee. In Table 3, the background data of these women are presented according to the type of organ complication at inclusion. The biobank recently restarted inclusions after the COVID-19 pandemic in March 2021 and will continue to include women according to the research questions and sample size described above.

## 5. Discussion

This project aims to establish a biobank and database for severe organ complications of pre-eclampsia. This is only feasible in LMIC where the incidence of pre-eclampsia and its complications are high. To our knowledge, the project is the first biobank of its kind in an LMIC, integrating different methods and engaging clinical and preclinical researchers to investigate the organ complications of pre-eclampsia. The project has a unique focus on improving the understanding of the pathophysiology, the possibility for prediction of organ complications, and over time, the hope for drug evaluation and drug discovery for pre-eclampsia with severe features.

This particular field of research is hampered by small retrospective studies that lack sufficient validation or power [21]. Organ complications of pre-eclampsia are complex and difficult to investigate due to their low incidence in high-income countries, their sudden onset, and the restriction often imposed by research methods in pregnant women. By using a database that adheres to recommended variables and biosamples in pre-eclampsia research, the results from this study can be merged with results from other studies. This will enable the investigation of infrequent rare outcomes by increasing sample size, this providing valuable scientific knowledge, and support to the women who are affected by this serious condition [17]. PROVE holds biological samples and data from special investigations such as MRI and cerebral blood flow measurements as well as detailed demographic data. Taken together, this will enable us to examine the disease phenotype deeply and achieve an improved understanding of the pathophysiology behind the various debilitating organ complications.

Another known biobank of pregnancy complication in an LMIC is PREPARE [22]. PREPARE collects biospecimens and clinical data from women with pre-eclampsia in Brazil and also uses the same recommended variables as PROVE does from the CoLab initiative [17]. The aim of PREPARE is to include a large sample size of women in order to validate existing biomarkers and diagnostic tools in an LMIC setting, whereas in PROVE, we have a smaller sample size, but we also perform special investigations, focusing on underlying pathophysiological mechanisms. These biobanks are complementary to each other and also enable the merging of data and biomarker results. Other examples of existing biobanks (mostly in HIC) are the Baby Biobank [23], Peribank [24], and IMPACT study [25] that focus on the prediction of disease, genetics, and microbiome.

Studies assessing neurological complications of pre-eclampsia are mostly small retrospective case-control and preclinical studies investigating cerebral blood flow alterations, cerebral biomarkers, MRI findings, and clinical signs and symptoms. Results indicate altered dynamic cerebral autoregulation and increased peripheral concentrations of cerebral biomarkers in women with pre-eclampsia, compared to normotensive women [19,20,26]. However, these results are from smaller populations and have not been investigated in women with clinical manifestations of cerebral complications such as eclampsia. In PROVE, we add knowledge to this field by adding similar investigations in a group of women with severe disease. Again, this should improve the understanding of the pathophysiology underlying cerebral oedema, eclampsia, and intracerebral haemorrhage in pre-eclampsia. Cerebral biomarkers and cognitive function deficits in previous reports have also mainly been based on women with less severe disease [20,26,27]. Results from PROVE will confirm or dismiss the role of cerebral biomarkers and cognitive function in relation to the severity of disease in a dose–response fashion. Clinical signs and symptoms are poorly investigated and in a recent systematic review by our group, we showed that clinical signs and symptoms currently used such as headache and visual disturbances are generally poor predictors of eclampsia, and included studies were mainly composed of case–control studies [28]. Our study collects signs and symptoms in a predefined protocol, enabling the discovery of new promising predictors of eclampsia, as opposed to predictors already collected in clinical practice. These data will be combined with data collected in a similar fashion in other countries such as Pakistan, Solomon Islands, and Sweden. MRI findings are predominantly retrospective studies in which the prevalence of cerebral oedema in eclampsia varies from 60 to 100%, and MRI has been performed mostly for by clinical indications. The prevalence of cerebral oedema in other severe forms of pre-eclampsia is still unknown [29,30]. Thus, there is a need for larger, studies incorporating prospectively collected information with predefined variables and systematically conducted investigations of the cerebral function in women with pre-eclampsia, with and without neurological complications.

Pulmonary oedema is characterised by fluid retention in the alveoli causing swelling of the lungs. Fluid is normally kept within the capillaries due to healthy endothelial cells and a balance between the opposing capillary hydrostatic pressure and colloid oncotic pressure. If this balance is deranged or the endothelial layer in the alveoli is disrupted, pulmonary oedema can follow [31]. Pulmonary oedema secondary to pre-eclampsia can theoretically be caused by any of these pathways, explained by increased hydrostatic pressures due to increased afterload and left ventricular diastolic dysfunction in combination with capillary leak and interstitial oedema [32,33,34]. There is a paucity of data regarding the pathophysiological pathways in pulmonary oedema and how to individualise treatment depending on the underlying causes such as heart failure treatment versus lowering of blood pressure and fluid restriction.

The diagnosis of pulmonary oedema in pre-eclampsia is based on clinical and radiological features, and echocardiography is not a prerequisite for diagnosis [31]. Thus, the contribution of the heart in pre-eclampsia complicated by pulmonary oedema remains largely unknown. There is, therefore, a need to evaluate diagnostic cardiac biomarkers and/or echocardiography in the management of women with pre-eclampsia and pulmonary oedema regarding the involvement of the heart to improve short- and long-term prognosis. Data from PROVE will contribute to this gap in knowledge by a deeper characterisation of cardiac tissue abnormalities, cardiac function, and cardiac biomarkers in women with pulmonary edema versus women with pre-eclampsia that is not complicated by pulmonary oedema and normotensive pregnancies, respectively.

In summary, PROVE aims to improve knowledge of the pathophysiology behind the development of severe organ complications of pre-eclampsia, enabling early identification and treatment and in addition, over time, identification of new drug targets. PROVE is open to all researchers after application to the research team and ethical approval. More information can be found at www.preeclampsiaresearch.com (accessed on 17 April 2021). Through the high-quality standardised collection of data and biosamples in accordance with the requirements of CoLab [17], PROVE will contribute to data- and biosample sharing in infrequent outcomes, enabling analyses of larger datasets. This is urgently needed in order to contribute to the sustainable development goals and improve women’s health.

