## 2. Aims and Objectives

To establish a pre-eclampsia database and biobank at Tygerberg Hospital, Stellenbosch University and to facilitate research in pre-eclampsia, detailed data are collected according to an international consensus of core predictors and outcomes in pre-eclampsia research [17]. The aims of this approach are to enable the discovery of possible predictors and diagnostic tools for organ complications in pre-eclampsia and to develop the understanding of the underlying pathophysiology further with a focus on different organ complications. We collect biological specimens including plasma, saliva, cerebrospinal fluid, urine, placenta, and umbilical cord blood (mixed venous–arterial). In subgroups, we perform specialised examinations to assess organ dysfunction, reveal underlying pathophysiological pathways, and aim to relate the findings to predictors and biomarkers. These examinations include cerebral magnetic resonance imaging (MRI), cardiac MRI, transcranial Doppler, echocardiography, and cognitive function testing.

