### 3.2. Collection of Clinical Information

Clinical information is collected on datasheets and entered into an online secure password-protected Research Electronic Data Capture (REDCap) database. The data collection includes information on the participant’s age, gravidity, parity, medical history, current pregnancy information, and outcome of the pregnancy. Only the principal investigators have access to patient identifying information and each participant is allocated a study number. The variables collected in the database correspond to the recommended core demographics, predictors, and outcomes listed in “*Strategy for standardization for pre-eclampsia research design*” by the international group Co-Lab for harmonisation of pre-eclampsia research (Table 1) [17]. The women are also interviewed at inclusion with a short questionnaire regarding signs and symptoms specific for pre-eclampsia (Table 1).

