
APGAR; appearance, pulse, grimace, activity, respiration, AST; aspartate transaminase, CFQ; Cognitive Failure Questionnaire, CPAP; continuous positive airway pressure, GCS; Glasgow Coma Scale, HELLP; haemolysis, elevated liver enzymes, low platelets, HIV; human immune deficiency virus, ICU; intensive care unit, LV; left ventricle, MoCA; Montreal Cognitive Assessment, MRI; magnetic resonance imaging, PPH; postpartum haemorrhage, PRES; posterior reversible encephalopathy syndrome. Nominal (n); binary (b); ordinal (o); continuous (c).

**Table 2 cells-10-00959-t002:** Biological samples collected for the PROVE biobank.

Type of Sample	Sampling	Volume	Tubes, Processing
Blood	At inclusion, at delivery, during hospital stay	Maximum of 12 mL/sample	EDTA plasma, spinned, 1 mL aliquots
Placenta: foetal surface	At delivery	RNAlater, 4 × 1 cm^3^	Removal of RNA later, 2 mL aliquots
Placenta: foetal surface	At delivery	Frozen sections 1 cm^3^	2 mL aliquots
Placenta: maternal surface	At delivery	RNAlater, 4 × 1 cm^3^	Removal of RNA later, 2 mL aliquots
Placenta: maternal surface	At delivery	Frozen sections 1 cm^3^	2 mL aliquots
Cord Blood (mixed venous–arterial)	At delivery	Maximum 12 mL	EDTA plasma, spinned, 1 mL aliquots
Urine	At inclusion	Maximum 12 mL	Sterile tube, spinned, 1 mL aliquots
Cerebrospinal fluid	At delivery	Maximum 2 mL	Sterile tube, spinned, 1 mL aliquots
Saliva	At inclusion	Stored in a 3 cc cup	2 mL aliquots

EDTA; ethylenediaminetetraacetic acid, RNA; ribonucleic acid.

**Table 3 cells-10-00959-t003:** Background characteristics of the women included in the biobank until March 2020, by complication at inclusion.

	Neurology *	Pulmonary Oedema	HELLP/Renal Impairment	Pre-Eclampsia **	Normotensive
***n***	86	43	23	54	38

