**OUTCOMES n (%)**					
**Severe hypertension**	35 (41)	29 (67)	16 (70)	14 (26)	0 (0)
**Eclampsia**	82 (95)	0 (0)	0 (0)	0 (0)	0 (0)
**Recurrent eclampsia**	26 (30)	0 (0)	0 (0)	0 (0)	0 (0)
**GCS < 13**	22 (26)	0 (0)	0 (0)	0 (0)	0 (0)
**Stroke**	3 (4)	0 (0)	0 (0)	0 (0)	0 (0)
**Blindness**	1 (1)	0 (0)	0 (0)	0 (0)	0 (0)
**Pulmonary oedema**	5 (6)	43 (100)	3 (13)	0 (0)	0 (0)
**HELLP**	19 (22)	7 (16)	22 (96)	1 (2)	0 (0)
**Renal impairment**	16 (19)	5 (12)	9 (39)	1 (2)	0 (0)
**Admitted to ICU**	10 (12)	6 (14)	1 (4)	0 (0)	0 (0)
**Postpartum haemorrhage**	9 (11)	3 (7)	2 (13)	3 (5)	2 (4)
**Intubation**	15 (17)	6 (14)	1 (4)	0 (0)	0 (0)
**Intrauterine foetal death**	12 (14)	8 (19)	7 (30)	5 (9)	0 (0)
**Venous thromboembolism**	2 (2)	1 (2)	0 (0)	0 (0)	0 (0)
**Abruptio placentae**	5 (6)	2 (5)	2 (9)	2 (4)	1 (3)

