**GOS at two months**					
Mild or no disability	63 (96)	33 (100)	10 (100)	42 (100)	26 (100)
Severe disability	1 (1)	0 (0)	0 (0)	0 (0)	0 (0)
Death	2 (3)	0 (0)	0 (0)	0 (0)	0 (0)
Missing	20	10	13	12	12

* Eclampsia, stroke, or blindness. ** Pre-eclampsia with or without acute severe hypertension, without organ complications. *** Missing values for BMI due to missing antenatal charts or antenatal charts without registration of BMI.; BMI, body mass index; GCS, Glasgow Coma Scale, GOS, Glasgow Outcome Scale, HELLP, haemolysis, elevated liver enzymes, and low platelets; HIV, human immunodeficiency virus; ICU, intensive care unit; continuous variables are presented as means with standard deviations. Categorical variables are presented as numbers with percentages.

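### Women with eclampsia appear to be enrolled after the fit, so for eclampsia the biobank can suggest candidate predictors but cannot support prospective prediction

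*Protocol article*

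**What the plan says.** Section 2 of the protocol article gives as an aim to "enable the discovery of possible predictors and diagnostic tools for organ complications in pre-eclampsia". The opening of the Discussion speaks of the possibility of predicting organ complications. Its paragraph on neurological complications notes that earlier evidence on symptoms came mostly from case-control studies and then states: "Our study collects signs and symptoms in a predefined protocol, enabling the discovery of new promising predictors of eclampsia".

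On timing, section 3.2 says: "The women are also interviewed at inclusion with a short questionnaire regarding signs and symptoms specific for pre-eclampsia". Sections 3.4.2 and 3.4.3 place brain MRI and the first transcranial Doppler at study entry, and Table 2 has blood, urine and saliva taken at inclusion. The title of Table 3 is "Background characteristics of the women included in the biobank until March 2020, by complication at inclusion", and its footnote defines the neurology group as "Eclampsia, stroke, or blindness". Under Power Calculations, the initial targets are 100 women with eclampsia, 50 with pulmonary oedema and 50 in each control group.

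**The concern.** A predictor has to be measured, or at least dated, before the event. If women with eclampsia enter the biobank after the seizure, whatever is measured at entry may reflect a cause of the fit, the post-ictal state, or treatment and delivery since then. The data cannot separate these.

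The symptom questionnaire does ask about the past, but Table 1 anchors that block to inclusion, not to the fit. Confusion, twitching, absent-mindedness and poor concentration are all on the list, and all can follow a seizure. Counted as warning symptoms, they would produce associations that arise from the event itself. A predefined form standardises the items but does not change when they are asked. The biobank is open to outside researchers, so a loose use of the word predictor would carry over into derived studies.

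**Working it through.** **1. Table 3 adds up.** 86 + 43 + 23 + 54 + 38 = 244, matching section 4 ("244 women have been included in the biobank"). Eclampsia in the neurology group is 82/86 = 95%, as printed.

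**2. When did the fit occur?** The neurology group has 82 women with eclampsia, 3 with stroke and 1 with blindness, and 82 + 3 + 1 = 86. If every woman in the group meets the footnote definition, the 4 without eclampsia account for all the stroke and blindness. The 82 then qualify through eclampsia alone, and the table title says that grouping is by complication at inclusion. Three other places agree:
- Table 1 lists the date of the convulsion, whether it was postpartum and where it happened among the inclusion variables.
- Table 1 asks for blood pressure, antihypertensive drugs and magnesium before the event or inclusion.
- Recruitment is to a quota of women with eclampsia.

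This is a strong inference. No sentence states it.

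**3. Eclampsia in the other groups.** Women with pre-eclampsia outside the neurology group: 43 + 23 + 54 = 120, with 0 recorded. Purely as arithmetic, the exact two-sided 95% upper limit is 1 − 0.025^(1/120) = 3.0%. It is not an incidence: sampling was by outcome, time at risk is not given, women may enter before or after delivery (section 3.1), and enrolment continues. A zero count is also unremarkable at low rates: at an assumed 1%, the chance of none in 120 is 0.99^120 = 30%.

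**4. What a case-control analysis can support.** Section 3.5 asks for at least 10 cases per variable: 82/10 gives about 8 variables, and the planned 100 gives 10. For one binary symptom, take 100 cases, 50 controls, a two-sided 5% test and an assumed odds ratio of 3. With control prevalence p0, case prevalence is p1 = 3p0/(1 − p0 + 3p0).

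| Assumed p0 | p1 | Power |
|---|---|---|
| 10% | 25% | 59% |
| 20% | 43% | 81% |
| 30% | 56% | 87% |

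Check of the first row: pooled prevalence (25 + 5)/150 = 0.20; null standard error √(0.16 × 0.03) = 0.0693; alternative standard error √(0.1875/100 + 0.09/50) = 0.0606; (0.15 − 1.96 × 0.0693)/0.0606 = 0.23, which gives 59%. Candidate finding is feasible.

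**5. Why absolute risk is out of reach.** Among 82 cases and the 120 other women with pre-eclampsia, the case fraction is 82/202 = 41%, which recruitment sets. With p0 = 20% and p1 = 42.9%, the apparent positive predictive value in the biobank is (82 × 0.429)/(82 × 0.429 + 120 × 0.20) = 35.1/59.1 = 59%. At an assumed true incidence of 1% it would be 0.00429/(0.00429 + 0.198) = 2.1%; at 3%, 0.01286/(0.01286 + 0.194) = 6.2%. The odds ratio is 3 throughout. Only outside incidence data can fix the absolute figure.

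**6. Timing of symptom items.** Table 1 records an onset time only for headache and visual disturbances. The other symptoms have none, so a symptom that began after the fit cannot be told from one that preceded it.

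**The case against.** The article's language is cautious: it speaks of possible or promising predictors and promises no prediction model, predictive value or absolute risk. Each derived study needs its own ethics approval. Table 1 does seek pre-event information: booking blood pressure and proteinuria, whether blood pressure was taken before or after the fit, and drugs given before the event. Pooling with other countries is planned. All of this stands, and it limits the point to what the data may be called and how symptoms are anchored. Pooling data gathered in a similar way adds size but does not by itself remove recall after the event.

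Four stronger readings are tempting, and the documents do not support them:
- **That the biobank can yield no predictors of eclampsia.** Dated chart values and symptoms recalled from before the fit can give candidates.
- **That 0 of 120 is a rate from which to size a prospective cohort.** It is an interim count without time at risk, and the article claims no such cohort for eclampsia.
- **That women with uncomplicated pre-eclampsia had almost no later complications.** That column lists 14 with severe hypertension, 5 foetal deaths, 3 postpartum haemorrhages, 2 abruptions, 1 HELLP and 1 renal impairment. Their timing is not given.
- **That a quarter of the interviews were with impaired women.** GCS below 13 (22/86 = 26%) and intubation (15/86 = 17%) are recorded as outcomes, not as states at interview, and competence to consent is required (for minors, assent with parental consent). Both use the whole neurology group as denominator. They justify a sensitivity analysis but do not measure faulty recall.

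**Conclusion.** The point holds in limited form. For eclampsia the biobank has the case-control structure that its own Discussion criticises. It supports hypothesis-generating, retrospectively recalled candidate predictors: about 8 variables from 82 cases, or 10 from the planned 100. It does not support prospective prediction of eclampsia or, without outside incidence data, absolute risks. Measurements at entry in these women follow the event and cannot separate cause from consequence, and most symptom items cannot be placed before or after the fit.

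This rests on reading the Table 3 title literally and on the inclusion form and recruitment targets. The article should confirm that enrolment follows the fit. Recurrent eclampsia (26 women) may include events after enrolment, but its timing is not given. The odds ratio, symptom prevalences and incidences used above are assumptions for illustration.

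**What to change.** **Wording.** In section 2, and in the opening and neurological paragraphs of the Discussion, reserve the word predictor for variables dated before the event or for complications shown to arise after enrolment. Describe measurements at or after the event as associated with eclampsia, or as diagnostic at presentation. State whether women with eclampsia are enrolled after the fit, and call the symptom findings hypothesis-generating.

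**Symptom questionnaire.** In women with eclampsia, count only symptoms with onset before the fit, and record onset for every item. Compare them with women who have pre-eclampsia without eclampsia, using a look-back window of the same length that ends at inclusion. Add a sensitivity analysis without women who had GCS below 13 or intubation; both fields are already collected.

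**Cost.** A more modest claim, an onset field on the form and slightly more analysis. For women already enrolled, items without an onset time may have to be set aside or reported as of uncertain timing.

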## Figures and Tables

**Figure 1 cells-10-00959-f001:**
[figure not shown]
Flow chart of the study.

**Table 1 cells-10-00959-t001:** Clinical information collected in the database RedCap.

Variables at Inclusion	Variables During Hospital Stay	Variables at Discharge and at 3 Months Follow Up
**Demographics** Age (c)	**Delivery details** Gestation at delivery (c)	**Discharge** Date of discharge (N/A)
Date of birth (N/A)	Indication for delivery (n)	Number of days in hospital (c)
Hospital folder number (N/A)	Mode of delivery (n)	Adverse maternal outcomes (n)
Address (N/A)	Place and supervision of delivery (n)	*Eclampsia*
Contact number (N/A)	Medication used before delivery (n)	*Recurrent eclampsia*
Race (n)	Maternal plasma sample taken (b)	*Severe hypertension*
Marital status (n)	Cerebrospinal fluid sample taken (b)	*Stroke*
Total years of full-time education (o)		*PRES syndrome*
Current job situation (n)	**Neonatal outcomes**	*Cortical blindness*
Current living situation (n)	Liveborn (b)	*Severe renal impairment*
Number of people cohabitating (o)	Sex (b)	*Dialysis*
Diagnosis at inclusion (n)	Intubation at birth (b)	*Pulmonary edema*
Singleton pregnancy (b) Plasma sample taken at inclusion (b)	Birth weight (c) APGAR score at 5 min (o)	*Inotropic support* *Signs of bleeding or DIC*
**Medical history** Gravidity (o) Parity (o) Number of miscarriages (o) Number of previous terminations (o) Outcome of previous viable pregnancies (n) Previous pre-eclampsia, number of times (o) Previous pre-eclampsia before 34 weeks (b) New paternity (b) Fertility treatment (n) HIV status (b) If HIV positive, viral load (c) Tobacco use (n) Alcohol use (n) Methamphetamine use (b) Diabetes (n) Previous cardiovascular disease (n) Chronic hypertension(b) If chronic hypertensive, number of medications (o) Anaemia (n) Neurological disease (n) Respiratory disease (n) Renal disease (n) Inflammatory bowel disease (b) Autoimmune disease (o) Depression (b) Heredity for pre-eclampsia (o) First degree relative with hypertensive disorders (b) Partner’s heredity for pre-eclampsia (b) Pre-pregnancy weight (c) Pre-pregnancy height (c) Antenatal care (n) Gestation at first presentation for antenatal care (c) Systolic blood pressure at booking (c) Diastolic blood pressure at booking (c) Proteinuria at booking (o) On hypertensive treatment at booking (b) Aspirin use in this pregnancy (b) Gestation aspirin was started (c) Calcium use in this pregnancy (b) Gestation calcium was started (c) Estimated due date (N/A) Estimated due date calculated by (o)	Cord blood taken (b) Neonatal outcome (n) **Placental outcomes** Placental sample taken (b) Date for placental sample (N/A) Placental weight (c) **Daily hospital forms** Days since admitted (n) Highest systolic blood pressure (c) Highest diastolic blood pressure (c) Lowest oxygen saturation (c) Highest respiratory rate (c) Intubated (b) CPAP (b) Antihypertensive medication (n) Magnesium sulphate (b) Nitroglycerin/Tridil (b) Diuretic (b) Special investigations performed (n) Seen by other specialities (n) Haemoglobin (c) Platelets (c) Urea (c) Creatinine (c) Arterial pH (c) Arterial pO2 (c) Arterial pCO2 (c) Arterial lactate (c) Magnesium (c) Blood taken for freezing (b) **Transcranial doppler** Date and time for examination (N/A) Oxygen saturation when start of measurement (c) Pulse at start of examination (c) Systolic blood pressure at start of examination (c) Diastolic blood pressure at start of examination (85) Oxygen (n) End-tidal CO_2_ (c) Magnesium sulphate at examination (b) Magnesium sulphate before examination (b) If yes, how many hours since finished (o) Nitroglycerin/Tridil at examination (b) Antihypertensive medication at examination (o)	*HELLP syndrome* *Liver enzymes > 500 IU/L* *Liver rupture or hematoma* *Admitted to ICU* *Maternal death* *PPH* *Laparotomy for any reason apart from caesarean section* *Glasgow Coma Score < 13* *Myocardial infarction* *Intubation* *Sepsis* *Coma* *Venous thromboembolism* *Intrauterine fetal death* *Perinatal or infant mortality* *Abruptio placenta* *Mild to moderate pre-eclampsia without complications* *None (pregnant control)* **Cognitive function testing** MoCa (scanned) CFQ (c) **Long-term outcome 3-12 months** Date (N/A) Neonatal death within 6 weeks after expected due date (b) Neonatal death at any point after discharge (b) Maternal systolic blood pressure (c) Maternal diastolic blood pressure (c) Is mother on blood pressure treatment (b) Final hypertensive diagnosis (n) Any persisting neurological symptoms (b) Glasgow Outcome Scale (o)
**Symptoms before inclusion** Edema (n) Visual disturbances (n) Time of onset for visual disturbances (n) Headache (n) Headache onset (n) Epigastric/abdominal pain (n) Tightness in the chest (b) Shortness of breath (b) Focal neurological deficits (n) Tendon reflexes (n) Nausea (b) Vomit (b) Confusion (b) Twitching or jerking arms or legs (b) People around her noticing that she was absent in mind (b) Difficulty concentrating (b) Speech affected (b) Hearing affected (b) Mood changes (n) Anxiety (b) Feel like end of the world was coming (b) Dizziness (b) Weakness/paralysis (b) Other symptoms not listed (free text) Highest blood pressure before inclusion /fit (c) Highest diastolic blood pressure before inclusion /fit (c) Blood pressure recorded before/after fit (n) Date of convulsion if applicable (N/A) Fitted postpartum (b) Proteinuria (o) Lowest platelet count (c) Highest AST (c) Lowest haemoglobin (c) Highest creatinine (c) Blood pressure medication before the event/inclusion (n) Magnesium sulphate before the event/inclusion (b) If eclamptic fit, where did it occur (n)	GCS score at examination (c) Neurological deficits at start of examination (text) Depth left side (c) Systolic velocity left side (c) Mean velocity left side (c) Diastolic velocity left side (c) Cerebral perfusion pressure left side (c) Autoregulatory index left side (c) Depth right side (c) Systolic velocity right side (c) Mean velocity right side (c) Diastolic velocity right side (c) Cerebral perfusion pressure right side (c) Autoregulatory index right side (c) **Brain MRI** MRI performed (b) Date of MRI (N/A) *MR data saved in the electronic radiology system for later entry* **Echocardiography and MRI heart** Diagnosis of pulmonary edema in relation to delivery (n) Date of echocardiography (N/A) Date of cardiac MRI (N/A) Inclusion criteria (o) If pulmonary oedema, how was diagnosis set (o) Blood sample (b) LV diameter in diastole (c) LV end-systolic diameter (c) Interventricular septal thickness in diastole (c) Posterior wall thickness in diastole (c) LV mass (c) LV mass index (c) Relative wall thickness (c) Left ventricular ejection fraction (by Simpson’s biplane) (c) Fractional shortening (c) Tissue doppler SA wave velocity (c) Myocardial performance index (c) Global longitudinal strain (c) Regional wall motion abnormalities (c) E wave height (c) A wave height (c) E:A ratio (c) E wave deceleration time (c) Isovolumetric relaxation time (c) E’ septal (c) E’ lateral (c) E’average (c) E:E’septal (c) E:E’lateral (c) E:E’average (c) Pulmonary vein pulse wave doppler (c) Left atrial diameter (c) Left atrial area (c) Left atrial volume (c) Left atrial volume indexed to BSA (c)	

APGAR; appearance, pulse, grimace, activity, respiration, AST; aspartate transaminase, CFQ; Cognitive Failure Questionnaire, CPAP; continuous positive airway pressure, GCS; Glasgow Coma Scale, HELLP; haemolysis, elevated liver enzymes, low platelets, HIV; human immune deficiency virus, ICU; intensive care unit, LV; left ventricle, MoCA; Montreal Cognitive Assessment, MRI; magnetic resonance imaging, PPH; postpartum haemorrhage, PRES; posterior reversible encephalopathy syndrome. Nominal (n); binary (b); ordinal (o); continuous (c).

**Table 2 cells-10-00959-t002:** Biological samples collected for the PROVE biobank.

Type of Sample	Sampling	Volume	Tubes, Processing
Blood	At inclusion, at delivery, during hospital stay	Maximum of 12 mL/sample	EDTA plasma, spinned, 1 mL aliquots
Placenta: foetal surface	At delivery	RNAlater, 4 × 1 cm^3^	Removal of RNA later, 2 mL aliquots
Placenta: foetal surface	At delivery	Frozen sections 1 cm^3^	2 mL aliquots
Placenta: maternal surface	At delivery	RNAlater, 4 × 1 cm^3^	Removal of RNA later, 2 mL aliquots
Placenta: maternal surface	At delivery	Frozen sections 1 cm^3^	2 mL aliquots
Cord Blood (mixed venous–arterial)	At delivery	Maximum 12 mL	EDTA plasma, spinned, 1 mL aliquots
Urine	At inclusion	Maximum 12 mL	Sterile tube, spinned, 1 mL aliquots
Cerebrospinal fluid	At delivery	Maximum 2 mL	Sterile tube, spinned, 1 mL aliquots
Saliva	At inclusion	Stored in a 3 cc cup	2 mL aliquots

EDTA; ethylenediaminetetraacetic acid, RNA; ribonucleic acid.

**Table 3 cells-10-00959-t003:** Background characteristics of the women included in the biobank until March 2020, by complication at inclusion.

	Neurology *	Pulmonary Oedema	HELLP/Renal Impairment	Pre-Eclampsia **	Normotensive
***n***	86	43	23	54	38
